### Therapist compliance with protocol

The SST will update a logbook after each SI session to record the following: participant progress, motivation, adherence to equipment, and emotional enagement. The SST will have monthly individual and 3-monthly group supervision sessions with the lead SST, who will oversee the delivery of the intervention across the five sites. The lead SST will review the SST logbooks to discuss at each supervision, and particpant details will be anonymised.

### Participant adherence to the intervention

Adherence to the use of sensory equipment and other intervention procedures will be documented by the PwD and companion in pre-printed diaries and in the SST logbook and willl be described during the post-intervention semi-structured interview. Details of how these data will inform analysis of process measures will be detailed in the process evaluation protocol article.

### Analysis of Outcomes: Descriptive analyses

Continuous and ordinal variables will be described in terms of absolute frequency, mean, standard deviation, 95% confidence interval of the mean, median, interquartile range, and minimum and maximum. Categorical variables will be described in terms of number, proportion and 95% exact binomial confidence interval of proportion.

### Quantitative analyses: Test of the intervention effect

For estimating and testing the effect of the intervention on the primary (DEMQOL score at 36 weeks) and secondary outcomes, an *a priori* Statistical Analysis Plan (SAP) will be devised, detailing the analysis methods, outcomes, covariates, handling of missing data, standard error estimation methods and any sensitivity analyses. The SAP will be submitted to the Trial Steering Committee (TSC) for review and approval prior to the start of statistical analyses. Intention-to-treat principles will be followed, and all randomly assigned participants will be analysed according to trial arm allocation, including as far as possible those who discontinue the study, for whom follow-up data will continue to be collected wherever possible.

A separate multi-level (participants within sites) mixed-effects regression analysis will be conducted for each outcome to estimate and test the mean effect of the intervention at 18 and 36 weeks. In each case, the dependent variable will be the outcome scores at baseline, 18 and 36 weeks, and covariates will be trial arm, time point and pre-specified participant- and country-level covariates. The tests for treatment effect at 18 and 36 weeks will be based on the relevant component of the trial arm by time-point interaction. Study site will be treated as a fixed effect. The primary analysis will use complete cases only; sensitivity analyses will assess robustness of results to concerns, including non-normality (using the non-parametric bootstrap method of standard error estimation), missing values (using single or multiple imputation as appropriate) and baseline imbalance (by inclusion of unbalanced covariates). Between-site heterogeneity in treatment effects will be explored by using moderator analysis. The statistics team at Manchester University will conduct all analyses using Stata statistical software [57]. All statistical tests will be performed with a two-sided type I error rate of 5%.

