#### Person with dementia inclusion criteria

Is at least 60 years old;is diagnosed with dementia in accordance with ICD-10 (10th revision of the International Statistical Classification of Diseases and Related Health Problems) criteria because of the following conditions: Alzheimer’s disease (AD) (in accordance with NINCDS-ADRDA [28] criteria) or vascular dementia (VAD) (in accordance with NINDS-AIREN [29] criteria) or “mixed” dementia (AD + VAD);has dementia in the mild to moderate stage, as indicated by a Montreal Cognitive Assessment (MoCA) [30] score of at least 10;if taking cognitive enhancing medication (that is, cholinesterase inhibitors or memantine), this must be on a stable, unchanged dose for at least 4 weeks prior to screening;has adult-acquired hearing or vision impairment (or both) defined by*vision impairment*: defined by the presence ofpresenting binocular visual acuity of not more than 6/9.5 and greater than 6/60 in Snellen metric (or at least + 0.2 logMAR [75 EDTRS Score] and less than + 1.0 logMAR [35 EDTRS Score]) using the Portable Eye Examination Kit (PEEK) vision tool [31] andvisual field greater than 10° using confrontation visual field test [32]

and/or*Hearing impairment*: defined by a bilateral hearing difficulty, indicated by failure of a pure tone hearing screening test in both ears, defined by hearing worse than 35 dBHL at 1000 Hz and above in the better ear, using the HearCheck device [33];lives in an ordinary community dwelling (including sheltered and very sheltered accommodation);is willing to accept SI;has a companion who fulfils the criteria below and is willing to participate in the study;has the capacity to provide informed consent to participate in the study or, if lacking that capacity, has a nominated consultee to provide consent on their behalf;speaks and understands the language of the intervention delivery, as determined by the investigator;is affiliated with a social security system (for France).

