### Sample size

The trial is powered to detect a standardised effect size of 0.267 (equivalent to a 4-point change) on the Dementia Quality of Life (DEMQOL) [42] and assuming a standard deviation of 15 points in DEMQOL [42] scores. In this population, this effect size is equivalent to the smallest change that could be considered clinically meaningful. Assuming a correlation of 0.6 between baseline and 36-week follow-up DEMQOL scores [42] and an attrition rate of 20% at follow-up (a conservative estimate based on the 12%–15% rates observed by Wenborn *et al*., 2008 [43]), the trial will need to recruit 354 participant dyads at baseline (177 per arm) in order to achieve 80% power to detect the aforementioned effect size at the two-sided 5% level of significance.

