#### Secondary outcomes

For the person with dementia:QoL assessed by DEMQOL at W18QoL assessed by DEMQOL Proxy, at W18 and W36, rated by the companionscores of the following measures at W18 and W36:○ functional ability, assessed by the following scales:▪ Bristol Activities of Daily Living scale [44];▪ Veterans Affairs Low Vision-Visual Functioning Questionnaire [45];▪ Veterans Affairs Low Vision-Visual Functioning Questionnaire Spousal rating [45];▪ Hearing Handicap Inventory for the Elderly [46];▪ Hearing Handicap Inventory for the Elderly Spousal rating [47].○ global cognitive functioning, using the MoCA scale [30].○ behavioural and psychological symptoms of dementia, assessed by the 12-item Neuropsychiatric Inventory [48].○ relationship with companion, assessed by the Relationship Satisfaction Scale [49].

For the companion:mental well-being and QoL using the 12-item General Health Questionnaire [50] and health utility using the Short Form-12 Health Survey [51] (Brazier and Roberts, 2004 [51]), at W36;scores of the following measures at W18 and W36○ companion experience, assessed by the Family Caregiving Role scale [52];○ relationship with PwD, assessed by the Relationship Satisfaction Scale [49];○ companion anxiety and depression, assessed by the Hospital Anxiety and Depression scale [53].

Health economic outcomes:health-care resource utilisation from baseline to W18 and W36 collected using the RUD-Lite instrument [40] with the companion;health utility, ascertained at baseline, W18 and W36 from:○ 5-level EuroQol 5-dimension rated by both the PwD and the companion [54];○ Short Form-12 Health Survey [51], rated by both the PwD and the companion.

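### The hearing and vision scales are to be analysed as one average over all randomised participants, which dilutes the test of hearing- and vision-related function

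*Protocol article*

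**What the plan says.** **Who enters.** Under Person with dementia inclusion criteria, a participant qualifies who "has adult-acquired hearing or vision impairment (or both". People with a single impairment are therefore enrolled by design.

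**What they receive.** Under Sensory intervention, stage 2, glasses, hearing aids or both are supplied according to each person's needs.

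**What is measured.** Secondary outcomes lists the "Hearing Handicap Inventory for the Elderly [46" (HHIE), the Veterans Affairs low-vision questionnaire (LV-VFQ) and a spousal rating of each, at weeks 18 and 36, with no restriction by type of impairment. Table 4 and Follow-up visits give every dyad the same battery.

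**How it is analysed.** Under Quantitative analyses: Test of the intervention effect, the article states: "A separate multi-level (participants within sites) mixed-effects regression analysis will be conducted for each outcome to estimate and test the mean effect". Both follow-up times are covered. The same section has all randomised participants analysed by allocated arm, with complete cases in the primary analysis. The only moderator analysis it names is by site. Covariates and sensitivity analyses are deferred to a statistical analysis plan (SAP), which is not available here.

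**The concern.** The second hypothesis under Research question defines functional ability partly through hearing- and vision-related daily activities. These four scales are its direct test. On the HHIE, participants enrolled for vision alone have, as a group, less hearing handicap to remove and less hearing correction to receive. The same holds on the LV-VFQ for those enrolled for hearing alone. Averaging over both kinds of participant shrinks the expected effect by an amount that depends on the case mix.

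This affects interpretation. A null HHIE result could mean that hearing support did not work, or that too few participants needed it. If the quality-of-life result is also null, these scales would help to separate failure to improve sensory function from improved function that did not raise quality of life.

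**Working it through.** **1. The plan's own figure.** Sample size states: "The trial is powered to detect a standardised effect size of 0.267 (equivalent to a 4-point change"; "assuming a standard deviation of 15 points in DEMQOL"; "Assuming a correlation of 0.6 between baseline and 36-week follow-up DEMQOL scores"; 20% attrition; "in order to achieve 80% power to detect the aforementioned effect size" "at the two-sided 5% level of significance".

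- Baseline-adjusted SD: 15 × √(1 − 0.6²) = 12.
- Evaluable per arm: 2 × [12 × (1.960 + 0.842) / 4]² = 141.28.
- Recruited per arm: 141.28 / 0.8 = 176.6, rounded up to 177, so 354 in total.

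The stated number reproduces. With 177 × 0.8 = 141.6 evaluable per arm, power on DEMQOL is 80.1%.

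**2. Dilution on a sensory scale.** The documents give neither the share p of participants with the relevant impairment nor the effect d (in SDs) among them. Both are varied below. Assumptions: zero effect in the others, equal SD in both groups, and the DEMQOL correlation (0.6) and attrition (20%) carried over to these scales. Residual variance is then 0.64 SD².

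- All participants: effect p × d, standard error √(2 × 0.64 / 141.6) = 0.0951.
- Impaired subset: effect d, standard error √(2 × 0.64 / (141.6 × p)).
- Power = Φ(effect / standard error − 1.96).

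Worked case, d = 0.4 and p = 0.5:

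- All: 0.20 / 0.0951 = 2.10; Φ(0.14) = 55.7%.
- Subset: 0.40 / 0.1345 = 2.97; Φ(1.01) = 84.5%.

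| d in impaired | p | effect in all | power, all | power, impaired subset |
|---|---|---|---|---|
| 0.267 | 0.5 | 0.133 | 28.9% | 50.9% |
| 0.267 | 0.7 | 0.187 | 50.1% | 65.0% |
| 0.267 | 0.9 | 0.240 | 71.4% | 75.8% |
| 0.4 | 0.5 | 0.20 | 55.7% | 84.5% |
| 0.4 | 0.7 | 0.28 | 83.8% | 94.1% |
| 0.4 | 0.9 | 0.36 | 96.6% | 97.9% |

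At p = 1 the two analyses coincide.

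**3. If the unimpaired also gain.** Let them gain a fraction f of d. The all-participant effect is d × [p + (1 − p)f]. The subset has more power when √p > p + (1 − p)f, that is, when f < √p / (1 + √p). The limit is 41% at p = 0.5, 46% at p = 0.7 and 49% at p = 0.9. Checks at d = 0.4, p = 0.5:

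- Gain of 0.1 SD (f = 25%): effect 0.25, power in all 75%, still below 84%.
- Gain of 0.2 SD (f = 50%): effect 0.30, power in all 88%, above 84%.

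**4. If the unimpaired vary less.** Keep d = 0.4, p = 0.5 and zero gain, and give the unimpaired one quarter of the residual variance.

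- Average residual variance: 0.64 × (0.5 + 0.5 × 0.25) = 0.40. Standard error √(0.80 / 141.6) = 0.0752, power 76%.
- Mixing two effects adds 0.5 × 0.5 × 0.4² = 0.04 to the intervention arm's variance. Standard error √(0.84 / 141.6) = 0.0770, power 74%.
- As the unimpaired variance approaches zero, the same two calculations give about 84% and 82%.

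Lower variance alone therefore closes the gap but does not reverse it.

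**The case against.** **This belongs to the SAP.** The article defers methods, outcomes, covariates and sensitivity analyses to a later SAP, and a subset defined at screening does not conflict with intention-to-treat. Part of this stands: the SAP may already restrict these scales, and whether to adjust for impairment type is a matter for it. However, the article itself states both the population and the mean-effect model for each outcome, and analysis populations are not among the items it defers. A SAP that followed the text would produce the diluted analysis.

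**The overall average is a legitimate target.** This also stands. In a pragmatic trial of an individualised package, the mean effect over everyone enrolled is a sensible quantity. A reader might infer that the all-randomised result is biased or uninterpretable. The documents do not support that: it is a valid randomised comparison, only less specific to the function being corrected.

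**Participants outside the criterion can still benefit.** A reader might infer that those without the relevant impairment cannot gain, or that vision-only participants never receive hearing correction. Neither is stated. All intervention participants get communication training and goal setting, and devices follow a full assessment. The hearing criterion requires failure in both ears, so people with one-sided or milder loss fall outside it and may still report handicap. Zero gain is thus an assumption, and the ranking reverses beyond the limits in step 3.

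**The power contrast is illustrative.** This is correct. The mix and the effect are assumed and the correlation is borrowed from DEMQOL. At p = 0.7 and d = 0.4 both analyses have more than 80% power.

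**Conclusion.** The point holds as an inexpensive improvement to secondary outcomes. As written, the plan tests the hearing and vision parts of the second hypothesis through an average that includes participants without the impairment each scale measures. That average is valid but diluted, and probably less powerful than an analysis in those with the impairment.

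Under the equal-SD, zero-gain assumptions with a 0.4 SD effect, power is 56% against 84% when half have the impairment, and 84% against 94% when 70% do. The true size cannot be found from the documents, because the mix is not given. The difference is negligible if nearly everyone has both impairments, narrows if the unimpaired vary less, and reverses if they gain more than about 41% (p = 0.5) to 49% (p = 0.9) of the impaired effect.

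It would be wrong to infer a flaw in the primary analysis. DEMQOL applies to everyone, its analysis is untouched, and the 354 reproduces.

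**What to change.** In Quantitative analyses: Test of the intervention effect, and in the SAP, pre-specify:

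- for the HHIE and its spousal version, the treatment effect among randomised participants who met the hearing criterion at screening;
- for the LV-VFQ and its spousal version, the treatment effect among those who met the vision criterion at screening;
- these analyses as the test of the hearing and vision parts of the second hypothesis, with the all-randomised result reported alongside.

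Participants with both impairments contribute to both sets. Status is recorded before randomisation, so the comparison within each set stays randomised. Allocation is stratified by centre only, so arm sizes within a set may differ somewhat by chance.

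The cost is wording and analysis time, with no new data. The downside is that these secondary results rest on fewer participants and apply only to people with the relevant impairment.

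### The primary test, as written, is a comparison of change from baseline with about 71% power; the stated 80% requires adjustment for baseline

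*Protocol article*

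**What the plan says.** The Sample size section plans for a 4-point difference in DEMQOL, "assuming a standard deviation of 15 points in DEMQOL" scores (standardised effect 0.267), and "an attrition rate of 20% at follow-up". It continues: "Assuming a correlation of 0.6 between baseline and 36-week follow-up DEMQOL scores". From these it concludes that 354 dyads, 177 per arm, are needed "in order to achieve 80% power to detect the aforementioned effect size at the two-sided 5% level of significance". It does not name the analysis on which the calculation rests.

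The section Quantitative analyses: Test of the intervention effect describes a mixed-effects regression in which "the dependent variable will be the outcome scores at baseline, 18 and 36 weeks, and covariates will be trial arm, time point", together with pre-specified participant- and country-level covariates. Site is a fixed effect. On the test itself it says: "The tests for treatment effect at 18 and 36 weeks will be based on the relevant component of the trial arm by time-point interaction". The primary analysis is limited to complete cases. Neither a common baseline mean across arms nor baseline DEMQOL as a covariate is mentioned.

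**The concern.** A correlation between baseline and follow-up can enter a sample-size calculation in two ways. If the follow-up score is adjusted for baseline, the outcome variance is multiplied by 1 − ρ². If change from baseline is compared, it is multiplied by 2(1 − ρ). The change-score factor is larger for any ρ below 1.

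The model described has the baseline score as an outcome row and trial arm as a term of its own, so each arm has its own baseline mean. The arm-by-week-36 interaction then measures how much more one arm changed than the other. If the sample size was derived under baseline adjustment, the two sections use different estimators and the trial has less power than it claims. The Sample size section treats 4 points as the smallest clinically meaningful change, so the cost is a higher chance of missing an effect that the investigators regard as worth finding.

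**Working it through.** **Inputs** (Sample size section): difference 4, SD 15, ρ = 0.6, attrition 20%, two-sided α = 0.05, power 80%, 177 per arm. Completers per arm: 177 × 0.8 = 141.6.

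**Formulas** (normal approximation, variance factor f):
- completers per arm: n = 2 × (1.96 + 0.8416)² × f / (4/15)²
- standard error: SE = 15 × √(2f/n)
- power = Φ(4/SE − 1.96)

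**Step 1: reproduce the plan's figure.** With baseline adjustment, f = 1 − 0.6² = 0.64 and n = 141.3. Then 141.3/0.8 = 176.6, rounded up to 177 per arm, 354 in total. This matches the protocol.

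**Step 2: identify the test described.** In balanced complete cases with a free arm term, the arm-by-week-36 coefficient is (week 36 − baseline mean in one arm) − (the same in the other). Its factor is f = 2(1 − 0.6) = 0.80. Time-constant covariates and a fixed site effect, entered as main effects, cancel out of a within-person change and do not reduce this variance.

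**Step 3: compare at 141.6 completers per arm.**

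| Analysis | f | SE | 4/SE | Power |
|---|---|---|---|---|
| Baseline-adjusted | 0.64 | 1.426 | 2.805 | 80.1% |
| Interaction as written | 0.80 | 1.594 | 2.509 | 70.8% |

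The variance ratio is 0.80/0.64 = 1.25. For 80% power the written test needs 176.6 completers per arm; 176.6/0.8 = 220.7, so 221 per arm, 442 in total.

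**Step 4: check with the three-time-point model.** A generalised least squares calculation, with week 18 included, gives SE 1.594 (70.8%) when the arm effect at baseline is free and SE 1.426 (80.1%) when it is set to zero. The results are the same with all correlations at 0.6 and with adjacent visits at 0.7 and baseline to week 36 at 0.6. The week-18 data therefore do not recover the loss in complete cases. Simulating change-score and baseline-adjusted tests at 142 per arm (20,000 runs) gave 70.6% and 79.6%.

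**Step 5: vary the assumptions** (other inputs unchanged).

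| Setting | Baseline-adjusted | As written |
|---|---|---|
| ρ = 0.5 | 73.6% | 61.2% |
| ρ = 0.7 | 88.1% | 82.6% |
| Attrition 15% | 82.4% | 73.4% |
| Attrition 12% | 83.7% | 74.9% |

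The written test reaches 80% with 354 dyads only if 2(1 − ρ) = 0.64, that is ρ = 0.68.

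**The case against.** The strongest reply is that the article does not settle the decisive detail. It gives no model equation, and a test on the arm-by-time interaction also fits a model in which the arms share a baseline mean. It defers methods and covariates to a statistical analysis plan that is not shown. If that plan constrains the baseline means or adjusts for baseline, power returns to 80.1%. This limits the finding to the model as described here. But the article already fixes the dependent variable, the arm term, the coefficient tested and the complete-case restriction. Listing trial arm as a covariate beside its interaction with time naturally means a free arm effect at baseline.

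Second, baseline adjustment in the sample size is inferred. Because 0.64/0.8 = 0.80, a change-score calculation with no attrition allowance also gives 177 per arm. That is correct, but the protocol says attrition is allowed for, and on that reading too the written test has about 71% power after 20% attrition.

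Third, the inputs are uncertain. The protocol calls 20% attrition conservative against observed rates of 12% to 15%, but at those rates power is still only 73% to 75%. Using all available rows instead of complete cases gives 72.6% if dropouts contribute baseline only, and 73.6% if every dropout also has week 18 and all correlations are 0.6. Only a higher correlation closes the gap, and 0.6 is the protocol's own value.

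Finally, the test is unbiased with a correct type I error rate in a randomised trial. That stands: this is a loss of efficiency, not of validity.

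**Conclusion.** The concern holds. On the protocol's own inputs, the analysis it describes has about 71% power for a 4-point difference, some 9 percentage points below the figure stated, and a false-negative risk of about 29% instead of 20%. The conclusion rests on three things: a free arm effect at baseline, which is the natural reading of the text; repeated scores from the same person being modelled as correlated; and ρ = 0.6. A correlation of 0.68 or more, or an analysis plan that constrains or adjusts for baseline, would remove the shortfall. None of the other alternatives considered does so. Because the trial's size is justified by a power that its stated primary analysis does not deliver, the two sections must be brought into line before the analysis plan is approved.

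**What to change.** Change one sentence in the analysis section, and carry it into the analysis plan, in either of two forms:

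- Keep baseline, week 18 and week 36 as outcomes but drop the trial-arm main effect, so that the arms share a baseline mean. Retain time point and the arm-by-week-18 and arm-by-week-36 terms, and test the latter for the primary outcome.
- Model only the week-18 and week-36 scores, with baseline DEMQOL as a covariate, and test the arm contrast at week 36.

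In complete cases the two have the same precision, and either gives 80.1% power with 354 dyads. They can differ when values are missing, so one should be named. Because the article applies the same model to every outcome, the chosen form should sensibly extend to secondary outcomes with a baseline value, although no power is claimed for them.

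If the unconstrained interaction is kept, the Sample size section should state the power as about 71%. Changing the model costs a sentence of wording and needs no further participants or data.

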### Randomisation and allocation concealment

Randomisation will be performed no later than 3 days following baseline. Randomisation will be conducted through the trial electronic case report form (eCRF) [55]. One person in each site will perform randomisation. One person from the research team will be identified in each site to perform randomisation, excluding the blinded researcher who will undertake the outcome visits. Randomisation will be stratified by centre. Once participants are allocated to the eCRF, eligibility criteria (including signed informed consent) must be met to allow for randomisation online. The SST will then trigger the local procedure for sensory assessment and provision of hearing aids/glasses for those participants allocated to the SI group.

The randomisation code will be maintained by the European Clinical Trials Platform & Development (EUCLID) Coordinating Trial Unit (CTU). The blinded researcher and the statistician team will not have access to the randomisation code. To ensure allocation concealment, full details of the randomisation scheme will not be disclosed.

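### With site and covariates entered as main effects, the stated model returns the raw difference in mean change at week 36, so the baseline-imbalance sensitivity analysis cannot show whether imbalance matters

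*Protocol article*

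**What the plan says.** All but one of the relevant statements are in the protocol article, section *Quantitative analyses: Test of the intervention effect*.

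- Outcome: "the dependent variable will be the outcome scores at baseline, 18 and 36 weeks".
- Predictors: "covariates will be trial arm, time point and pre-specified participant- and country-level covariates".
- Test: "The tests for treatment effect at 18 and 36 weeks will be based on the relevant component of the trial arm by time-point interaction".
- Site: "Study site will be treated as a fixed effect". It is also the randomisation stratum (section *Randomisation and allocation concealment*): "Randomisation will be stratified by centre".
- Analysis set: "The primary analysis will use complete cases only".
- One listed sensitivity analysis concerns "baseline imbalance (by inclusion of unbalanced covariates".

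The only interaction named in the treatment-effect model is arm by time. The section leaves further detail on covariates and sensitivity analyses to a statistical analysis plan, which is not shown.

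**The concern.** Trial arm has its own main effect, so the arms are free to differ at baseline, and the treatment effect is a difference between differences: week 36 minus baseline. A covariate entered once, with one coefficient for all time points, cannot alter such a contrast when every participant has all three scores. Adding unbalanced covariates this way must return the primary estimate.

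Two things are at stake. The trial could report its result as robust to baseline imbalance on the strength of a check that could not have come out otherwise. And a reader would take the primary test to be adjusted for site and the pre-specified covariates when, for the week 36 effect, it is not.

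**Working it through.** **1. Inputs and the plan's own figure.** Section *Sample size* gives SD 15, a 4-point target, correlation 0.6 between baseline and week 36, 20% attrition, 80% power and two-sided 5%.

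- Baseline-adjusted SD: 15 × √(1 − 0.6²) = 12.
- Per arm: 2 × (1.960 + 0.842)² × 12² / 4² = 2 × 7.849 × 9 = 141.3.
- With attrition: 141.3 / 0.8 = 176.6, so 177 per arm and 354 in total, as stated.
- Expected completers: 354 × 0.8 ≈ 283.

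The sample size therefore rests on the variance factor of an analysis that conditions on baseline, 1 − 0.6² = 0.64. The stated test is a change contrast.

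**2. Algebra.** Let D(t) be the raw difference in arm means at time t, x a baseline covariate with a single coefficient b, and Δx its difference in means between arms. The adjusted arm difference is D(t) − bΔx at every t. The tested effect is

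[D(36) − bΔx] − [D(0) − bΔx] = D(36) − D(0),

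which is the difference in mean change, whatever b and Δx are. The same holds for site indicators. It does not depend on the covariance structure, because the equations for change contain only arm.

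**3. Numerical check.** Three complete-case data sets were simulated: 142 per arm, five sites, and a covariate with a deliberate 0.4 SD imbalance that lowers week 36 change by 3 points per SD. Random-intercept models were fitted by REML.

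| Data set | Difference in mean change | Arm × time | + site | + site + covariate | Covariate × time added |
|---|---|---|---|---|---|
| 1 | 0.35388 | 0.35388 | 0.35388 | 0.35388 | 1.87939 |
| 2 | 2.57684 | 2.57684 | 2.57684 | 2.57684 | 3.27239 |
| 3 | 1.42649 | 1.42649 | 1.42649 | 1.42649 | 2.61779 |

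The first three models also agree in standard error to about 1e-5 (data set 1: 1.68554, 1.68553, 1.68553). Generalised least squares with an unstructured covariance, on a further data set, gave −0.28732 (SE 2.02971) with no covariates, with site, and with site and covariate.

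The covariate-by-time term moves the estimate by 1.53, 0.70 and 1.19 points. The expected shift is 0.4 × 3 = 1.2.

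**4. Size of what is missed.** Shift = (imbalance in SD) × (points of week 36 change per SD).

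- 0.1 SD and 2 points per SD: 0.2 points, or 5% of the 4-point target.
- 0.2 SD and 5 points per SD: 1.0 point, or 25% of the target.

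These inputs are assumptions; the article gives none. For scale, the SD of change is 15 × √(2 × (1 − 0.6)) = 13.4 if the SDs are equal at both times, so 5 points per SD means a correlation with change of 5/13.4 = 0.37. With 142 per arm the standard error of a standardised difference is √(2/142) = 0.119, so a chance imbalance of at least 0.2 SD (z = 1.69) has probability of about 9% per covariate.

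**5. Where exactness ends.** Among completers after covariate-dependent dropout (23% to 26%), estimates with and without the covariate were again identical (0.72961, 2.09712, 1.98381). With partial records kept, adding the covariate moved the estimate by +0.006, −0.219 and +0.177. These shifts come from missingness. If an added covariate has missing values, the complete-case set changes and the estimate can move for that reason alone.

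**The case against.** The strongest objection is that the article never says covariates enter only as main effects. It speaks of including them and leaves covariates and sensitivity analyses to the analysis plan, which may specify time interactions or a baseline-conditional model. The planned moderator analysis by site would itself need site-by-time terms, and the sample size implies baseline adjustment. This stands as a limit: the point is about the protocol text. It does not remove the point, because that text fixes the outcome vector, the arm main effect, the contrast, the complete-case set and the form of the check. A plan that follows it literally inherits the problem.

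A second objection is that little may be lost. Much of this also stands. A covariate that shifts DEMQOL equally at all times is already subtracted out, so only predictors of change are missed. Large site imbalance is unlikely because randomisation is stratified by centre. The precision forgone from covariates is small: in one simulated trial of 283 participants the SE fell from 1.732 to 1.684, under 3%, with the interactions added. In the three data sets above, with their deliberate imbalance, it rose slightly (data set 1: 1.686 to 1.735).

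Two stronger readings are tempting. A reader might infer that the primary estimate is biased. The documents do not support that: under randomisation the difference in mean change is unbiased in expectation with respect to baseline imbalance. A reader might also say that the check fails to detect imbalance. Its stated purpose is robustness of the result, not detection; what it cannot do is show whether imbalance affects the estimate.

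**Conclusion.** The point holds for the model as worded. With complete records, no missing covariate values and main-effect entry, site, the pre-specified covariates and any unbalanced covariates leave the week 36 effect exactly unchanged. The imbalance sensitivity analysis is redundant for imbalance in level and blind to imbalance in factors that predict change, so its agreement with the primary result would carry no information. The missed shift is 0.2 to 1 point in the two assumed scenarios; no figure in the documents pins it down. This is a defect in a named robustness check and in the stated adjustment. It does not invalidate the primary comparison, and the unseen analysis plan may already resolve it.

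**What to change.** Amend the model description in *Quantitative analyses: Test of the intervention effect*, and carry it into the analysis plan, by one of two routes.

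- **Preferred:** model the week 18 and week 36 scores with baseline score, site and covariates as predictors, each with an effect free to differ by time point. The imbalance check then adds further covariates in the same way. This also matches the 0.64 variance factor behind 354.
- **Alternative:** keep the stated model and enter site and every covariate with its time-point interaction, in both the main and the imbalance sensitivity model.

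These are different estimators. Adding the covariate in a baseline-adjusted week 36 analysis of the three data sets gave 1.129 to 1.474, 5.217 to 4.796 and 3.707 to 3.629, so in the second the shift had the opposite sign to that in the interaction model. One route should be fixed before the analysis. Inclusion as a main effect should not be described as a check on baseline imbalance.

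The cost is one or two sentences and a few degrees of freedom: in the alternative model, 8 for site by time (4 × 2) and 2 per further one-parameter covariate, among about 283 completers.
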